#### Exercise professionals (PARS group only)

Exercise professionals (e.g. physiotherapists, sport and exercise therapists) will be recruited using various strategies. An overview of all facilities related to PA promotion (physiotherapy practices, rehabilitation sports, prevention sports and fitness facilities related to health promotion) in the Nürnberg metropolitan region has already been compiled. The study team will systematically contact the responsible staff of each facility via telephone to present the study as well as general conditions and ascertain levels of interest. If the facility staff express interest, the responsible exercise professionals will participate in a 1.5-day digital training course in which they are familiarised with the intervention (individual PA promotion and assessments) and will have the opportunity to try out motivational interviewing. The study team will also advertise the project through project stakeholders’ websites, newsletters and information letters to the stakeholders’ members.

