### Randomisation, allocation and blinding

A cRCT with randomisation at the physician practice level will be conducted for organisational reasons and to avoid the risk of mixing participants from both groups within a medical facility (contamination). The research team will recruit the physicians and provide them with detailed information about the study or answer questions. After physicians express interest in participating in the study and meet the inclusion criteria, they must provide written informed consent, which needs to be supported by the cooperating health insurance company. Each medical practice will be randomly allocated to the PARS or PAA group using computer-based block randomisation (Excel 2016). Due to the local density of physician practices in the Nürnberg metropolitan region, six blocks for randomisation will be defined (Nürnberg city [*n* = 10], Nürnberg surrounding area [*n* = 2], Fürth city [*n* = 10], Fürth surrounding area [*n* = 2], Erlangen city [*n* = 10] and Erlangen surrounding area [*n* = 2]). The practices will then be informed about further procedures, and physicians, as well as medical staff working in the facility, will undergo specific training according to the assigned intervention arms.

Because of group-specific procedures and the corresponding training, blinding the participating actors (physicians, exercise professionals) is not possible in this study. However, blinding participants is possible due to randomisation on the physician practices’ level. The participants will only be informed about the intervention in which they are involved and will not come into contact with the other intervention arm during the study. The statistician will also be blinded to the group allocation until completion of the statistical analysis.

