#### Physical activity advice (PAA)

After being screened for eligibility, the PAA group will receive similar brief PA advicePAA to the PARS group. However, instead of being referred to exercise professionals for a more intensive intervention, the PAA participants will then receive a brochure with PA information, steps to start PA and adopt a more active lifestyle, specific information about the diseases targeted in this study and concrete tasks. The brochure also contains materials on BCTs, in which the BCTs ‘goals and planning’, ‘feedback and monitoring’ and ‘shaping knowledge’ are used but to a lesser extent than in the PARS group. The major difference between the two groups is the social support from an exercise professional, which is not available in the PAA group. An overview of the integrated BCTs for the PAA group is included in Additional file 2.

Like the PARS group, the PAA group will also receive the overview of local PA offers. A baseline questionnaire and follow-up questionnaire to be completed after 12 and 24 weeks will be sent by mail with stamped envelopes for their return to the project team. If the questionnaire has not been answered after 14 days, participants will receive a reminder by mail. If participants in this intervention arm have any questions about the brochure or completing the questionnaires, they can contact the research team by phone or email in specific time slots.

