### Ethics and dissemination

The ethics application for *BewegtVersorgt* was submitted in written form to and approved by the responsible FAU institution (committee reference number 110_21 B). Any changes made to the study after the review will be reported immediately. The pragmatic trial adheres to the Declaration of Helsinki, and the data will only be published in pseudo-anonymised form to ensure that no assignment to persons can take place. Data protection rules will be respected throughout the project’s duration, and all participating actors and patients will be informed in advance about the study and required to give their written informed consent to participate. They will have the option of revoking this consent at any time without giving reasons. The study results will be published in peer-reviewed journals and presented at national and international congresses. Regarding dissemination and scaling-up strategies, the transfer and scaling-up of the referral scheme (national level, other target regions and groups) will be discussed in a working group of national experts. However, as the planning of the scaling-up process depends on the results of the effectiveness analysis and the implementation success, it can only be concretised at a later stage in the project.

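### Participants are described as blinded, but they know the intervention they receive; at most they are not told about the comparator, and both primary outcomes are self-reported

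*Protocol article*

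**What the plan says.** Under Randomisation, allocation and blinding, the protocol article first says of the providers that "blinding the participating actors (physicians, exercise professionals) is not possible in this study". It then contrasts the participants with them: "However, blinding participants is possible due to randomisation on the physician practices’ level". Two reasons follow: "The participants will only be informed about the intervention in which they are involved", and they "will not come into contact with the other intervention arm during the study".

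The arms are described under Interventions. PARS participants have a 45-minute initial assessment, six 60-minute sessions and a 45-minute final assessment with an exercise professional. PAA participants receive a brochure after the physician's advice. The section on PAA says: "The major difference between the two groups is the social support from an exercise professional, which is not available in the PAA group".

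The primary outcomes are physical activity by the BSA-F questionnaire, which the first primary hypothesis itself labels as subjective, and PAHCO by questionnaire. Quality of life (EQ-5D-5L) is also self-administered. According to Data collection and management and the two intervention sections, the same exercise professional collects the PARS data at all three time points and may assist with questions. PAA questionnaires are sent and returned by post.

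**The concern.** A participant who has been told what they are receiving is not blinded to it. Expectation, and the wish to report progress to someone who has given support, act through knowledge of the treatment received. They do not need knowledge of the alternative. The reason given, randomisation by practice, addresses mixing of arms within a practice and not masking.

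This matters because the effectiveness conclusion rests on self-reports. If the statement is carried into the trial report, a positive result will appear to come from a trial with blinded participants. A reader would then give too little weight to reporting bias. Because questionnaires are collected differently in the two arms, such bias could act more strongly in PARS than in PAA.

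**Working it through.** **Step 1. What participants know.** The relevant statements, side by side:

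- Participant blinding is said to be possible because practices are randomised (Randomisation, allocation and blinding).
- Participants are told their own intervention (same section, next sentence).
- The arms differ in something no participant can miss: personal sessions with a professional, or none (Physical activity referral scheme; Physical activity advice).
- Patients are told about the study beforehand: "all participating actors and patients will be informed in advance about the study and required to give their written informed consent to participate" (Ethics and dissemination). How much this reveals about the other arm is not stated.

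The second and third items rule out masking to the treatment received. What can remain is unawareness of the comparator.

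**Step 2. Where this meets the outcomes.** Both primary outcomes and quality of life are completed by the participant. In PARS, the person who collects the forms and may help with them delivers the intervention and is unblinded. In PAA, no provider is involved in returning the forms. The route from knowledge of treatment to recorded outcome is therefore open, and it differs by arm.

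**Step 3. Contact between arms.** The article gives an assurance but no safeguard behind it. Practices are randomised within six local blocks, so both arms will ordinarily operate in the same towns. General practitioners and specialists are both recruited. Contact is possible on these facts, but no passage documents it.

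**Step 4. Scale, as an illustration.** Inputs from Sample size: 567 participants, 24 practices, α = 0.0125, power 80%, f = 0.175, ICC 0.02, drop-out 10%. Assumptions: two-sided tests (not stated in the article), equal arms, equal practice sizes and a normal approximation.

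The plan's own figure first:

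- d = 2f = 0.35. Two independent groups need 366 in total.
- Analysed: 567 × 0.9 = 510.3, or 510.3/24 = 21.26 per practice.
- Design effect: 1 + (21.26 − 1) × 0.02 = 1.405.
- 366 × 1.405 = 514.3, and 514.3/0.9 gives 572, within 1% of the stated 567. Taking 20 per practice gives 562. The inputs are read correctly.

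Standard error and critical value:

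- Effective N = 510.3/1.405 = 363.
- SE(d) = 2/√363 = 0.105.
- Two-sided critical value at 0.0125: z = 2.498.
- Power at d = 0.35 is 79.9%, as planned.

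With no true effect and a purely differential reporting shift b (in SD), the rejection rate per test is 1 − Φ(2.498 − b/0.105) + Φ(−2.498 − b/0.105):

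| Assumed shift b | Share of planned d = 0.35 | Rejection rate per test |
|---|---|---|
| 0 | 0% | 1.25% |
| 0.05 | 14% | 2.3% |
| 0.10 | 29% | 6.2% |
| 0.15 | 43% | 14.3% |
| 0.20 | 57% | 27.7% |

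The document gives no value for b. The table shows how sensitive the tests would be to a shift, not what the shift is.

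**The case against.** The strongest reply is that the article explains its own term at once. The sentence after the blinding claim says that participants know their own intervention, and the activity outcome is openly called subjective. A careful reader is not misled, masking someone to personal support versus a brochure is not feasible, and unawareness of the comparator may give some limited protection, for example against disappointment in PAA. Most of this stands: the term is disclosed as it is used, and no design change is called for. It does not make blinding the right word.

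Three stronger readings are tempting, and the document does not support them.

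- *That the protocol claims blinding protects the self-reported outcomes.* No passage says so. A reader might infer it from the word, but it is not stated.
- *That participants can be shown to meet the other arm.* A reader might point to "The study team will also advertise the project through project stakeholders’ websites, newsletters and information letters to the stakeholders’ members" or to "Like the PARS group, the PAA group will also receive the overview of local PA offers". The first stands in the section on recruiting exercise professionals for PARS, and nothing says the advertising describes two arms to patients. The second is an intended part of both interventions: the overview lists regional offers, and entry to PARS is by the physician's referral form. A PAA participant who joins a local class is following the PAA intervention. Enrolment of one patient through two practices is conjecture.
- *That the rejection rates measure this trial's bias.* They rest on assumed shifts, would apply to any unmasked trial of this precision with self-reported outcomes, and are not altered by rewording.

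**Conclusion.** The statement that participants can be blinded is wrong as written. They know the intervention they receive, and the most that can be said is that they are not told about the comparator. This rests on the article's own text and needs no assumption. Because the primary outcomes and quality of life are self-reported and are collected differently by arm, differential expectation and reporting bias is not excluded, and the trial should not be presented as participant-blinded.

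The size of any bias is unknown. The figure of about 6% per test for a 0.1 SD shift is an illustration under the stated assumptions. The no-contact assurance is unsupported, but it is not shown to be false. The sample size and the planned analysis are unaffected.

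**What to change.** Replace the sentence on participant blinding with: *participants are not blinded to the intervention they receive; they are only not informed about the comparator.* Report the trial as unblinded for participants. State with the results that the self-reported primary outcomes are open to expectation and reporting bias, and mention the different mode of questionnaire collection in the two arms. Either name the safeguard behind the no-contact statement or word it as an expectation.

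Optionally, add one item to the 24-week questionnaire on awareness of the other programme, and report it descriptively by arm. It should not define a subgroup or an exclusion, since awareness and contact arise after randomisation and use of local offers is part of PAA.

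The cost is a few sentences and, if wanted, one questionnaire item. The downside is a less favourable statement on blinding.

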### Interventions

The intervention period will last 24 weeks for the individual participant and will take place in the primary care setting of the German healthcare system. Both groups (PARS and PAA) will receive brief PA advice about increasing their activity levels. The study design is shown in Fig. 2. All trained actors in both groups will be asked to adhere to the intervention guidelines. For this, there are checklists to be completed and all participating actors as well as the participants are subsequently questioned about compliance. Participants are asked to maintain their lifestyle and not to start any other activities besides the study. Participants of both groups can quit the intervention at any time without giving any reason.

#### Physical activity referral scheme (PARS)

The PARS pathway is based on a conventional prescription for physical therapy in Germany and includes key actors, such as physicians, exercise professionals and exercise organisations. A detailed description of the pathway according to the PARS reporting checklist by Hanson et al. [28] can be found in Additional file 1.

The referral scheme begins with the physician’s screening. During a routine medical visit, the patient’s eligibility for participation in the study will be assessed. For this purpose, in addition to the inclusion and exclusion criteria described earlier, a short screening questionnaire will be used to determine average weekly PA. The questionnaire is based on three validated questionnaires for evaluating activity levels subjectively (Single-item [29], Physical Activity Vital Sign (PAVS) [30], Kaiser Permanente Southern California Exercise Vital Sign [31]) and is adapted to the trial setting. If the questionnaire reveals suitability – that is, the patient is inactive (< 150 min/week of moderate to vigorous PA) – brief PA advice (10 min) follows. The main goal is to initially motivate patients to change their behaviour and participate in the following intervention. The referral form can then be used to transfer the patient to a participating exercise professional.

After a 45-min initial assessment by the exercise professional, which is also part of the intervention, individually targeted PA promotion takes place over six sessions of 60 min each. The focus is on working out PA preferences with the patient, trying them and planning their subsequent implementation (e.g. in a regional exercise programme). For this purpose, exercise professionals can use a set of behavioural change techniques (BCTs), following Mitchie et al. [32], which has been identified as effective for PA behavioural change [33]. The BCTs are described in detail for both groups in Additional file 2. Exercise professionals in this study will focus particularly on the techniques of ‘goals and planning’, ‘feedback and monitoring’, ‘social support’, ‘shaping knowledge’ and ‘self-belief’. During the fourth session, a transfer to existing exercise or PA offers in the region will occur. Via a comprehensive brochure (more than 1000 offers from approximately 300 exercise providers), sorted by postal codes and types of offer, the participants will receive an overview of health-related PA opportunities and find the contact details for the respective exercise providers. After 12 weeks, a 45-min final assessment will take place to reflect on changes in the participant’s PA level and PAHCO and to formulate new goals for the next 12 weeks. The attending physician will receive feedback on the patient’s development. The transfer to existing PA programmes or independent activities will enable long-term maintenance of an active lifestyle, assessed in a follow-up assessment after a further 12 weeks. Before each assessment, participants will receive baseline or follow-up questionnaires to evaluate the effectiveness of the intervention and success of its implementation from their perspective. The questionnaires can be completed independently, although the treating exercise professional can assist with any questions.

#### Physical activity advice (PAA)

After being screened for eligibility, the PAA group will receive similar brief PA advicePAA to the PARS group. However, instead of being referred to exercise professionals for a more intensive intervention, the PAA participants will then receive a brochure with PA information, steps to start PA and adopt a more active lifestyle, specific information about the diseases targeted in this study and concrete tasks. The brochure also contains materials on BCTs, in which the BCTs ‘goals and planning’, ‘feedback and monitoring’ and ‘shaping knowledge’ are used but to a lesser extent than in the PARS group. The major difference between the two groups is the social support from an exercise professional, which is not available in the PAA group. An overview of the integrated BCTs for the PAA group is included in Additional file 2.

Like the PARS group, the PAA group will also receive the overview of local PA offers. A baseline questionnaire and follow-up questionnaire to be completed after 12 and 24 weeks will be sent by mail with stamped envelopes for their return to the project team. If the questionnaire has not been answered after 14 days, participants will receive a reminder by mail. If participants in this intervention arm have any questions about the brochure or completing the questionnaires, they can contact the research team by phone or email in specific time slots.

### Outcome measures

Except for participant characteristics, all data will be collected at the following three time points: after brief PA advice by the physician (basal), at 12 and at 24 weeks.

#### Participant characteristics

Participants’ characteristics will be captured through questions about age, gender, birthplace, marital status, social status, education level and income in the baseline questionnaire. Medical health status (type of disease) and medication intake will also be queried. Further specific medical characteristics prone to PA interventions, such as HbA1c, cannot be captured via questionnaires. For organisational reasons, these data cannot be retrieved systematically from all participating practitioners.

### Primary outcomes

#### Physical activity (PA) level

PA level will be measured by the Physical Activity, Exercise and Sport Questionnaire (Bewegungs- und Sportaktivität Fragebogen; BSA-F 3.0 [34]) – a validated German questionnaire that assesses the respondent’s amount of PA during the last four weeks. Based on the Frequency-Intensity-Time-and-Type (FITT) principles [35, 36], the questionnaire differentiates between leisure and transportation activities (PA score) and sport- and exercise-related activities (sport score). Participants report the frequency and duration of activities executed during the last four weeks. Minutes of leisure-time PA per week and sport-/exercise-related activity per week are calculated to gain the PA and exercise scores, which are combined to give the overall PA volume.

#### Physical activity (PA)-related health competence

Changes in PAHCO will be measured using the German version of the Physical Activity-Related Health Competence Questionnaire (BGK Questionnaire) [12, 37]. The questionnaire consists of 42 items that measure the following three sub-competencies necessary for health-promoting PA behaviour: movement competence (18 items; min = 0, max = 17.6), control competence (10 items; min = 0, max = 10.8) and self-regulation competence (14 items; min = 0, max = 14.8). Higher scores indicate higher competencies.

### Secondary outcomes

The European Quality of Life – 5 Dimensions – 5 Level (EQ-5D-5L) questionnaire is a self-administered quality of life scale that consists of a descriptive system and a visual analogue scale [38]. The descriptive system contains five well-being dimensions: mobility, self-care, usual activity, pain/discomfort and anxiety/depression, each of which has five levels of severity (no problems to incapacitated/extreme problem), coded from one to five. The result is a five-digit code that represents the participant’s health profile. The visual analogue scale assesses the participant’s overall current health.

In addition to the EQ-5D-5L results, the following secondary outcomes will be collected:Self-efficacy towards PA (SSA scale) [39]Participant’s perceived autonomy support (HCCQ-D) [40]Stage of change [41]Sport- and movement-related self-concordance (SSK scale) [42]

### Evaluation of the implementation plan

As well as effectiveness, the degree of implementation will be examined (see hypothesis 4) based on the five dimensions of the RE-AIM (Reach-Effectiveness-Adoption-Implementation-Maintenance) model [43], which include different aspects of implementation status and success at the individual and organisational levels. To examine the degree of implementation, a mixed method approach will be used, drawing on quantitative (e.g. characteristics of participating actors [Adoption] and patients reach [Reach]) and qualitative measurement procedures (e.g. adherence to guidelines [Implementation], adjustments during intervention [Implementation] and adoptions for long-term use [Maintenance]). For this purpose, a plan will be developed to capture various aspects in each dimension using different methods (e.g. interviews, focus groups, online surveys and document analysis) and at different moments during the intervention period. The perspectives of both the participating actors and patients will be addressed. Focusing on Patient-Reported Experience Measures (PREMs) [44], the patients’ perspectives will be retrieved with questionnaire surveys after 12 and 24 weeks, after which interviews or focus groups with patients may also be conducted. The actors will be asked for their perspectives during and after the interventions.

